### Secondary efficacy endpoints

The statistical analysis plan (SAP) highlights three key secondary endpoint variables; number of migraine days, headache intensity and number of 30% responders. Other secondary endpoint variables in this study are cumulative hours of moderate and severe pain intensity, days with rescue medication and quality of life measures. Several prespecified exploratory endpoints will also be analysed, including number of crystal-clear headache-free days, number of 50% responders, 75% responders and 100% responders, change in autonomic symptoms and patient-reported outcomes questionnaires.

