**Sample size**

The MiBlock trial has a confirmatory statistical strategy that pre-specifies just one single hypothesis related to the primary endpoint. To that end, the sample size was calculated by a professional, independent biostatistician based on the data from the pilot study.
^
18
^ The standard deviation (SD) for the change in number of headache days per week between baseline and week 5 – 8 was 7. To detect a difference of 3.5 moderate to severe headache days per month between active and placebo groups in weeks 5 – 8, provided 80% power to reject the null hypothesis at 5% level nominal of significance and assuming a drop-out rate of 25%, a total of 170 patients will be randomised to treatment in this study. The chosen effect size was informed by results from the pilot study and by a clinical assessment of what would constitute a clinically meaningful benefit, particularly in light of the invasive nature of the treatment procedure.

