### Statistical analysis

The main analysis is planned when all participants have concluded the 12-week follow-up after the injection and the database has been locked. All statistical analyses are pre-planned and will be described in a SAP finalised prior to data lock. The SAP will also include a preplanned order for data analysis, as well as the results table templates for the blinded analysis. The order of data analysis is defined a priori in order to ensure that the main efficacy analyses are completed without the risk of unblinding which may occur when analysing the safety data.

The full analysis set (FAS) will include all randomised participants who received the injection. To adhere to the intention-to-treat ideal for the FAS population, participants that undergo unsuccessful injections (i.e. Investigative medicinal product (IMP) not administered bilaterally or unilaterally) are included in the FAS.

The FAS will be used for all efficacy analyses. Briefly, for the primary outcome, a mixed logistic regression model will be used to estimate the difference in the change from baseline in mean monthly headache days between the treatment and placebo group. The model will include the presence or absence of headache on each day with recorded information from baseline until 12 weeks after the injection as a dependent binary variable, treatment allocation, time-period (baseline, week 1-4, week 5-8 and week 9-12) and an interaction term between treatment allocation and post-injections time-periods are included as categorical fixed effects, and with participant ID as a random effect. Site of inclusion will also be assessed as a potential random effect prior to unblinding of the statistician to treatment allocation. All available data will be included in this analysis, regardless of proportion of eDiary days completed. The model works under the assumption that data are missing at random. No formal missing-not-at-random analysis are preplanned.

The analysis of secondary outcomes will use the same strategy, although using mixed linear regression models for continuous outcomes. Additionally, sensitivity analyses for the primary and secondary outcomes will be performed, which will include restriction analysis to the subgroup of participants with technically successful bilateral injections and the per-protocol
set. Analysis across all three postintervention 28 day periods will be performed, to allow evaluation of temporal patterns of treatment response.

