For responder endpoints, responder status is defined based on the percentage change in the number of moderate to severe headache days, comparing each 28-day post-intervention period with the 28-day baseline period. To reduce the risk of uncertainty or misclassification of responder status due to incomplete data, responder endpoints will be calculated only for participants who have completed at least 90% of daily headache diary entries in both 28-day periods used for the respective comparisons.

Prespecified subgroup analyses will be conducted for each of the following baseline factors: sex, baseline medication overuse, patient-reported accompanying cranial autonomic symptoms during migraine attacks, and concomitant use of preventive treatments targeting the CGRP system.

A prespecified assessment of the success of the double blinding is included in the SAP and will be included in the statistical analysis report. The assessment will use the blinding index proposed by Bang et al.
^
32
^ In addition, the blinding index proposed by James et al.
^
33
^ will be calculated, and the results will be compared as recommended by Bang et al.
^
32
^

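### Responder endpoints, including the key secondary 30% responder rate, are limited to participants with at least 90% diary completion, which conflicts with using the full analysis set for all efficacy analyses

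*Protocol article*

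**What the plan says.** All references are to the protocol article.

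- **Analysis set (Statistical analysis).** "The full analysis set (FAS) will include all randomised participants who received the injection", including those whose injection was technically unsuccessful. "The FAS will be used for all efficacy analyses".
- **Secondary outcomes (same section).** "The analysis of secondary outcomes will use the same strategy, although using mixed linear regression models for continuous outcomes".
- **Responder endpoints (same section).** Response is a percentage change in moderate to severe headache days between baseline and each 28-day period after injection. The population rule is that "responder endpoints will be calculated only for participants who have completed at least 90% of daily headache diary entries in both 28-day periods" being compared. The reason given is "To reduce the risk of uncertainty or misclassification of responder status due to incomplete data".
- **Status of the endpoint (Secondary efficacy endpoints).** The three key secondary variables are "number of migraine days, headache intensity and number of 30% responders". The 50%, 75% and 100% responder rates are exploratory.
- **Per-protocol criterion (Subject adherence, protocol deviations and violations).** Diary adherence below 90%, assessed per 28 days, is a protocol violation and removes a participant from the per-protocol analysis. The Statistical analysis section lists the per-protocol set among the sensitivity analyses.
- **Missing data.** The primary model assumes data are missing at random, and no formal missing-not-at-random analysis is planned.

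**The concern.** The general rule and the responder rule cannot both hold as written. One keeps every randomised and injected participant in every efficacy analysis. The other removes those with incomplete diaries from a whole class of efficacy endpoints, and the text does not call this an exception.

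The main responder analysis therefore applies the diary criterion that the plan otherwise reserves for a sensitivity analysis. The planned per-protocol analysis cannot show what that criterion does, because it applies the same cut-off. No responder analysis that keeps the excluded FAS participants is described.

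Whether a participant completes the diary after injection can depend on benefit, on side effects or on a guess at allocation. The Discussion accepts that effects such as facial weakness or diplopia may unblind. A participant who stops recording for any of these reasons is not counted against either arm but simply disappears. At stake is whether one of the three key secondary results is still a comparison of the groups as randomised.

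**Working it through.** **Inputs from the article.** 170 to be randomised; 1:1 allocation, so 85 per arm; 25% drop-out; 90% diary threshold; 28-day periods. Response rates and exclusion shares by arm are not given, and those used below are assumptions.

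**1. The plan's own figure.** The Sample size section uses a difference of 3.5 days, SD 7, 80% power and a 5% level, "assuming a drop-out rate of 25" per cent. By the normal approximation, n per arm = 2 × (1.960 + 0.842)² × (7/3.5)² = 62.8, so 63 per arm and 126 in total; 126/0.75 = 168. The t-test version needs 63.77 per arm, and 2 × 63.77/0.75 = 170.0. The stated 170 is reproduced, taking the SD and the difference on the same monthly scale. No sample size or power is stated for the responder endpoints.

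**2. What the threshold means in days.** 0.90 × 28 = 25.2, so 26 entries are needed (26/28 = 92.9%; 25/28 = 89.3% fails). Three missed days in either period exclude a participant. The eDiary accepts the present day and the two before it, so one five-day lapse loses three days, unless the paper back-up for technical problems applies.

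**3. How many might leave the denominator.** If the planned drop-out all falls before or during weeks 5-8 and leaves those participants short of 26 entries, 0.25 × 170 = 42.5. About 43 would be removed and about 127 would remain, roughly 64 per arm. The true number could be lower, because someone who stops after week 8 still counts for weeks 5-8. It could be higher, because participants who stay in the trial but miss three or more days are also removed.

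**4. Illustration with no true effect.** Assume 40% true response in both arms of the FAS and that every excluded participant is a non-responder. The reported rate is 0.40/(1 − share excluded).

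- Excluded 25% v 25%: 0.40/0.75 = 53.3% in both arms, no spurious difference.
- Excluded 30% v 20%: 0.40/0.70 = 57.1% v 0.40/0.80 = 50.0%, a spurious 7.1 points.
- Excluded 35% v 15%: 0.40/0.65 = 61.5% v 0.40/0.85 = 47.1%, a spurious 14.5 points from unrounded rates.

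Swapping the arms reverses the sign.

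**5. Illustration with one completer result.** Assume 50% v 30% among those retained, a 20-point difference. If the excluded are counted as non-responders, the rate is the retained rate × (1 − share excluded).

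- Excluded 25% v 25%: 37.5% v 22.5%, 15 points.
- Excluded 35% active v 15% placebo: 32.5% v 25.5%, 7 points.
- Excluded 15% active v 35% placebo: 42.5% v 19.5%, 23 points.

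The same completer result is thus compatible with quite different FAS results, and the planned analyses described in the article would not tell them apart.

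**The case against.** The rule is specified in advance, is specific to one class of endpoint and gives a reason. It can be read as describing evaluable participants within the FAS. That is a fair account of the intent, but the text does not say so, and prespecifying a selected comparison does not restore the protection of randomisation.

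Several counter-arguments stand and limit the point:

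- **The all-available-data sentence.** A reader might take "All available data will be included in this analysis, regardless of proportion of eDiary days completed" as a second contradiction. It refers to the primary model only. The conflict is with the general FAS sentence and the sentence on secondary outcomes.
- **The baseline part of the rule.** Baseline entries precede randomisation, and diary adherence is reviewed at visit 2 before allocation. Excluding on baseline completion narrows the population and costs precision, but does not bias the randomised comparison. Only the post-injection part carries the selection risk.
- **Unscaled counts.** A reader might infer that missing days among those retained are treated as headache-free. The article speaks of the number of days and is silent on scaling to days recorded. That derivation is commonly left to the SAP, which is not shown, so this is not a finding.
- **Lost precision.** A reader might infer that the fix recovers the precision lost with a smaller denominator. Imputation cannot recreate information from people with no diary data, so most of that loss would remain.
- **Safeguards.** The three-day entry window, the adherence dashboard and the paper back-up should limit missing days. They do not prevent drop-out.
- **Stakes.** The single confirmatory hypothesis is on the primary endpoint. No 90% rule is stated for the other two key secondary variables.

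**Conclusion.** The conflict in the text is certain. The FAS is said to serve all efficacy analyses, yet every responder endpoint is restricted by the per-protocol diary cut-off, and no analysis of the full FAS is described for them. The 30% responder rate is the endpoint of most consequence.

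The size of any bias is not known. It depends on how many participants are excluded, on whether exclusion differs by arm and on whether it is related to response; the article gives none of these. The figure of about 43 of 170 rests on all planned drop-out falling before or during weeks 5-8. The 14.5-point spurious difference rests on assumed rates and on every excluded participant being a non-responder. With no true effect, equal exclusion produces no spurious difference, and exclusion unrelated to outcome costs only precision. A reader might infer that the rule favours onabotulinumtoxinA; nothing in the article supports a direction.

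The primary endpoint is unaffected. The change should be made, but the primary result does not depend on it.

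**What to change.** Reconcile the two statements by making the FAS the main population for all responder endpoints:

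- Impute missing diary days under the same missing-at-random assumption as the primary model, and derive responder status from the completed 28-day counts.
- Add a sensitivity analysis that counts participants without usable data as non-responders.
- Keep the analysis of participants with at least 90% completion as supplementary, labelled as such.

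If the sponsor keeps the restriction as the main analysis, the least that is needed is an explicit exception to the FAS rule, together with a responder sensitivity analysis that retains all FAS participants.

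The cost is SAP wording and some imputation programming; no new data are needed. The main result would then rely on the missing-at-random assumption, as the primary analysis already does. The article says that the SAP will be finalised before data lock and does not say that lock has taken place. If it has, the FAS analysis should be reported beside the planned one.

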### Study monitoring

The study is monitored by independent monitors according to a monitoring plan developed based on their own project risk analysis. In addition, two independent, unblinded monitors are assigned to the two injection sites to monitor the drug accountability log.

An independent data safety monitoring committee consisting of one consultant anaesthesiologist with previous service on ethical boards, one neurologist with headache sub-specialisation and one biostatistician will assess safety at 10%, 25%, 50% and 75% of treated participants and advise the sponsor on the safety profile.

### Data access

Upon data lock following study completion, only the blinded study statistician will have access to the complete dataset, in accordance with procedures prespecified in the SAP. Once the analyses outlined in the SAP have been completed, the full dataset will be made available to all study investigators to facilitate preparation of the results for publication and to allow their independent review of the data. No contractual or other restrictions apply to this process, beyond compliance with applicable data protection regulations.

### Dissemination

The results of this trial will be published in international open access peer-reviewed medical journals and presented at relevant scientific meetings. The SAP and statistical analysis report will be made available upon publication. Publication will adhere to the Vancouver guidelines.

## Discussion

To the best of our knowledge, MiBlock is the first study to evaluate the efficacy of a bilateral onabotulinumtoxinA blockade towards the SPG in a treatment-resistant chronic migraine population. The eligible study participants represent a heavily burdened patient population in need of novel treatment approaches. Despite recent progress in treatment options, including monoclonal antibodies and gepants targeting the CGRP system, a significant proportion is still inadequately relieved of their migraine. For them, blockage of synaptic transmission in the SPG and thus modulation of the trigemino-autonomic reflex constitutes a novel treatment approach. Pilot studies in both cluster headache and chronic migraine show an acceptable safety profile and promising efficacy data.
^
18,
21
^ Recently published real-world data from an open-label treatment setting suggest that the therapeutic effect may be sustained over repeated injections, further supporting the rationale for evaluating this approach in a placebo-controlled trial.
^
19
^

This study is designed to allow a robust evaluation of efficacy. To address the presumed important placebo-response associated with interventional procedures, a placebo arm is required in addition to a resilient quadrupled blinding scheme. A residual risk of unblinding due to the occurrence of adverse events (interpreted as possible onabotulinumtoxinA effects), such as transient facial weakness or diplopia, unfortunately, cannot be avoided. To explore their effect on the blinding regimen, data to assess the blinding is collected at the final study visit.

Additional strengths of the study include precise targeting of the SPG, applying commercially available navigation systems in clinical use, and designated consultant neurosurgeons performing the procedure at two sites.

This study protocol has several limitations. First, the trial is designed to assess the efficacy and safety of a single-session intervention in a rigorously controlled setting, and therefore does not address questions related to the efficacy and safety of repeated injections.

The fixed dose of 25 IU onabotulinumtoxinA per side (total dose 50 IU) was based on results from pilot studies.
^
18,
21
^ A negative trial result may reflect underdosing or insufficient exposure, rather than absence of biological efficacy. Accordingly, future studies may need to explore repeated injections or dose-escalation strategies. An exploratory endpoint assessing the presence of cranial autonomic symptoms (rhinorrhoea, nasal congestion, and tearing, prospectively recorded in the eDiary) is included to evaluate whether signs of altered parasympathetic output can be detected, independent of changes in headache outcomes. If the trial demonstrates efficacy, it is not designed to elucidate the exact underlying mechanisms of action, which would require further dedicated investigation.

Participants may continue CGRP-targeting preventive treatments provided dosing has been stable for at least five months prior to inclusion and criteria for chronic migraine are still met. As the afferent arm of the trigemino-autonomic reflex is a site of action for CGRP, it cannot be excluded that ongoing modulation of the CGRP system may interact with SPG-targeted treatment, which targets the efferent branch of the same reflex arc. To address this potential limitation, a prespecified subgroup analysis comparing participants using versus not using CGRP-targeting preventive treatments is included.

The eligibility criteria inevitably limit the generalisability of the findings. Patients continuing PREEMPT- onabotulinumtoxinA treatment and patients who have experienced substantial frequency reduction with CGRP-targeting therapies (i.e., no longer meeting criteria for chronic migraine) are excluded. However, as the treatment strategy under investigation would most likely be considered for patients with insufficient response to PREEMPT and CGRP-targeting therapies, the study population is intended to reflect the clinical population most likely to be eligible for this intervention.

Conversely, patients with documented failure of more than six preventive medications are excluded to avoid inclusion of individuals with an extremely refractory phenotype, in whom treatment effects may be difficult to detect. While this approach limits generalizability, it is intended to reduce the risk of obscuring a potential treatment effect. The applicability of the findings to more refractory populations would need to be addressed in future studies should this trial demonstrate efficacy.

The study design poses ethical challenges as participants are required to keep their preventive medication stable during their trial participation, with a 50% chance of receiving placebo. In the design of the study care has been given to provide sufficient and standardised information to eligible candidates, underscoring these issues and allowing sufficient time to reflect on their decision to participate.

## Study status

The date of first enrolment was 25.10.2019, but with significant delays in recruitment from March 2020 due to the COVID-19 pandemic, including the need to temporarily close the inclusion. Recruitment ended February 2025.

## Ethical consideration

The disease burden of this pain condition renders this group vulnerable, underscoring the importance of properly conducted trials. Several measures are taken to ensure that patients are sufficiently informed before consenting to trial participation. Patients receive written information that includes the possibility of not having an effect of the IMP (or receiving placebo), and the possible complications of the intervention, prior to the first visit. A scripted review of study information with illustration is provided by investigators to all participants at visit 1, prior to providing informed consent. Participants were informed that the study protocol does not include an extension phase and that no opportunity for repeated treatment is provided within the framework of this study. All participants gave written informed consent before any study procedures were initiated.

Participants are insured through the Norwegian pharmaceutical liability Insurance (Legemiddelansvarsforsikringen) and the Norwegian System of Patient Injury Compensation (Norsk pasientskadeerstatning).

The trial adheres to the Declaration of Helsinki. The study protocol and the informed consent forms was reviewed and approved by the Norwegian ethics committee (ref 2018/2161, date of approval 8
^th^ of February 2019) and the Norwegian medical agency (ref nr. 18/16600-11, date of approval 20
^th^ of august 2019) prior to study initiation. Substantial amendments to the protocol are subject to review prior to implementation.

[name] (2025). Table 1, Eligibility criteria for participation in the MiBlock trial. figshare. Journal contribution.
https://doi.org/10.6084/m9.figshare.28930940.v1

## Data Availability

No data is associated with this article. 1.Figshare: Table 1, Eligibility criteria for participation in the MiBlock trial,
https://doi.org/10.6084/m9.
figshare.28930940.v1
^
34
^
This project contains the following underlying data:
Table 1Data is available under
CC BY 4.0 license2.Figshare: SPIRIT MiBlock.pdf,
https://doi.org/10.6084/m9.figshare.28806617.v1
^
35
^
This project contains the following underlying data:SPIRIT checklistData is available under
CC BY 4.0 license3.Figshare: Informed consent form - the Miblock trial,
https://doi.org/10.6084/m9.figshare.28806665.v1
^
36
^
This project contains the following underlying data:Consent formData is available under
CC BY 4.0 license4.Figshare: Informed consent form (english translation) - The MiBlock trial,
https://doi.org/10.6084/m9.
figshare.29165627.v1
^
37
^
This project contains the following underlying data:Translation of consent formData is available under
CC BY 4.0 license Figshare: Table 1, Eligibility criteria for participation in the MiBlock trial,
https://doi.org/10.6084/m9.
figshare.28930940.v1
^
34
^ This project contains the following underlying data: Table 1 Data is available under
CC BY 4.0 license Figshare: SPIRIT MiBlock.pdf,
https://doi.org/10.6084/m9.figshare.28806617.v1
^
35
^ This project contains the following underlying data: SPIRIT checklist Data is available under
CC BY 4.0 license Figshare: Informed consent form - the Miblock trial,
https://doi.org/10.6084/m9.figshare.28806665.v1
^
36
^ This project contains the following underlying data: Consent form Data is available under
CC BY 4.0 license Figshare: Informed consent form (english translation) - The MiBlock trial,
https://doi.org/10.6084/m9.
figshare.29165627.v1
^
37
^ This project contains the following underlying data: Translation of consent form Data is available under
CC BY 4.0 license
